## Abstract

**Background:**

Overdoses due to non-medical use of prescription opioids and other opiates have become the leading cause of accidental deaths in the USA. Buprenorphine and extended-release naltrexone are key evidence-based pharmacotherapies available to addiction treatment providers to address opioid use disorder (OUD) and prevent overdose deaths. Treatment organizations’ efforts to provide these pharmacotherapies have, however, been stymied by limited success in recruiting providers (physicians, nurse practitioners, and physician assistants) to prescribe these medications. Historically, the addiction treatment field has not attracted physicians, and many barriers to implementing OUD pharmacotherapy exist, ranging from lack of confidence in treating OUD patients to concerns regarding reimbursement. Throughout the USA, the prevalence of OUD far exceeds the capacity of the OUD pharmacotherapy treatment system. Poor access to OUD pharmacotherapy prescribers has become a workforce development need for the addiction treatment field and a significant health issue.

**Methods:**

This cluster randomized controlled trial (RCT) is designed to increase buprenorphine and extended-release naltrexone treatment capacity for OUD. The implementation intervention to be tested is a bundle of OUD pharmacotherapy capacity building practices called the Prescriber Recruitment Bundle (PRB), which was developed and piloted in a previous statewide buprenorphine implementation study. For this cluster RCT, organizational sites will be recruited and then randomized into one of two arms: (1) control, with treatment as usual and access to a website with PRB resources, or (2) intervention, with organizations implementing the PRB using the Network for the Improvement of Addiction Treatment organizational change model over a 24-month intervention period and a 10-month sustainability period. The primary treatment outcomes for each organizational site are self-reported monthly counts of buprenorphine slots, extended-release naltrexone capacity, number of buprenorphine patients, and number of extended-release naltrexone patients.

This trial will be conducted in Florida, Ohio, and Wisconsin, resulting in 35 sites in each arm, for a total sample size of 70 organizations.

**Discussion:**

This study addresses three issues of substantial public health significance: (1) the pressing opioid misuse epidemic, (2) the low uptake of OUD treatment pharmacotherapies, and (3) the need to increase prescriber participation in the addiction treatment workforce.

**Trial registration:**

ClinicalTrials.gov NCT02926482,

## Background

Overdoses due to non-medical use of prescription opioids and other opiates have become the leading cause of accidental deaths in the USA [1]. Opioid use disorder (OUD) pharmacotherapies are a key evidence-based intervention available to specialty addiction treatment organizations to address the increase in OUDs and reduce overdose deaths [2–4]. This study focuses on two of these pharmacotherapies, buprenorphine and extended-release naltrexone. Buprenorphine is an opioid agonist therapy that binds to the opioid receptor to reduce the effects of opioids. Buprenorphine enhances retention in treatment and reduces self-reported use of opioids, criminal activity, and mortality [3, 5, 6]. Buprenorphine can only be prescribed by health care providers who have completed training to obtain a waiver to treat a limited number of patients [7]. Patients take the medication daily via tablet or film formulations; a longer-acting implant formulation is also available. Extended-release naltrexone (Vivitrol®) is an opioid antagonist medication that blocks the opioid receptor and also has improved retention rates when compared to placebo [4, 8]. Extended-release naltrexone is typically injected once a month at prescriber’s office location. While these pharmacotherapies hold great promise, they are underutilized in OUD treatment. Of the 2.5 million Americans 12 years of age or older with OUDs [9], fewer than 128,000 of those attending specialty treatment programs had treatment plans that included pharmacotherapy [10].

Treatment organizations’ efforts to provide OUD pharmacotherapies have been hindered by limited success in recruiting providers to prescribe these medications. In previous studies [11], physician prescribers have expressed hesitancy to prescribe OUD treatment pharmacotherapies due to feeling that treating OUD patients can be difficult, limited confidence in treating OUD patients, lack of institutional support, inadequately trained staff, time constraints, poor reimbursement rates, and regulatory barriers to OUD pharmacotherapy [11–15]. One regulatory barrier specific to buprenorphine requires prescribers to apply for a waiver that limits them to treating 30 patient slots in year 1, 100 slots in year 2, and up to 275 slots per year thereafter. Legislation passed in 2016 expands prescribing privileges to advanced practice registered nurses and physician assistants, who must also complete training and obtain a waiver to treat a limited number of patients [16].

These conditions have created significant barriers to OUD treatment capacity and implementation of these pharmacotherapies. A recent analysis found that 24.1% of specialty treatment organizations using buprenorphine pharmacotherapy had to turn patients away due to insufficient prescribing capacity [17]. About 43% of the US counties have no buprenorphine prescribers; among states and the District of Columbia, 96% had OUD rates that exceeded their buprenorphine capacity [18].

Poor access to prescribers of OUD pharmacotherapy has become a workforce development need in the addiction treatment field. Traditionally, organizations providing addiction treatment services have not developed competency in recruiting prescribers; rather, they have primarily relied on a clinical workforce of counselors. That is quickly changing, as addiction treatment providers are now being called upon to expand their clinical services into physician-supported areas such as primary care, mental health/psychiatry, and pharmacotherapy for addiction disorders. This study protocol’s aim is to address this emerging need by testing a bundle of practices, the Prescriber Recruitment Bundle (PRB), coupled with the Network for the Improvement of Addiction Treatment (NIATx) organizational change model to increase OUD treatment pharmacotherapy workforce capacity.

The PRB was developed to address the leading barrier to buprenorphine implementation, lack of physician prescribing capacity, as identified by 40 treatment organizations participating in the Ohio project titled “To Test a Payer/Treatment Agency Intervention to Increase Use of Buprenorphine.” This was a surprising finding because lack of reimbursement for buprenorphine was expected to be the most frequent and challenging barrier to expanding buprenorphine use. However, as the project proceeded and reimbursement barriers were removed, the lack of physicians to prescribe buprenorphine prevented its use within treatment organizations. As a result, different interventions began to be tested to increase buprenorphine prescriber capacity. The successful interventions were packaged into what became the PRB and later were tested by eight organizations in the project. The eight organizations that applied the PRB increased buprenorphine prescribing slots by 48.3–100%. The slots, once acquired, were mostly filled due to the pressing need for medication-assisted treatment services. The PRB pilot recruited 10 new physicians and increased buprenorphine prescribing slots across the eight organizations by more than twofold. The PRB developed and piloted was limited to a pre/post-evaluation on a convenience sample; this protocol will describe a randomized test of the PRB.

### Objectives

In this cluster randomized controlled trial (RCT), the primary aim is to test the impact of the PRB implemented in conjunction with the NIATx organizational change model, relative to the control, on (a) increasing the number of buprenorphine treatment slots and extended-release naltrexone capacity and (b) increasing the number of patients receiving buprenorphine and extended-release naltrexone in the participating addiction treatment organizations. A secondary aim is to test whether the PRB affects factors likely to be associated with prescriber recruitment, including resources dedicated to prescriber recruitment and physicians’ job satisfaction [19–21], and subsequently, whether these factors mediate the effects of the PRB on key outcomes. Lastly, qualitative methods will be used to study the context and processes that influence PRB adoption and fidelity, to develop a deeper understanding of how the PRB influences recruitment beyond the quantitative study variables, and to gain knowledge of what organizational processes contribute to successful licensed prescriber recruitment.

## Methods

### Trial design

In the intervention arm of this cluster randomized trial, the PRB will be implemented during a 24-month trial using the evidence-based NIATx organizational change model developed by our research center. The control arm will only receive access to the PRB materials online via a secure website. Organizations in the control arm will complete all the same data collection instruments as those in the intervention arm.

### Participants

We selected the three states (FL, OH, and WI) due to the states’ varied frequency of opioid analgesic prescribing and drug-poisoning deaths [22, 23]. These states offered a mix of urban and rural settings, presence of minority populations, strength of data collection and reporting systems, and representation of both Medicaid expansion and non-expansion states.

In all three states, recruitment began with surveying all publicly funded organizations that are licensed to provide addiction treatment services and have at least 100 admissions per year. The state-based addiction treatment authorities provided a list of the organizations meeting these eligibility criteria. The survey assessed the organizations’ interest in increasing their buprenorphine prescribing capacity. Organizations expressing the need for greater OUD pharmacotherapy capacity were recruited into the trial through an invitation from the study team. Of 125 organizations indicating need for greater OUD pharmacotherapy, 24 organizations from Florida, 23 from Ohio, and 23 from Wisconsin agreed to participate, for a total of 70 organizational sites (Fig. 1, consort diagram). Thirty-five were placed in the intervention arm, and 35 were in the control arm.

**Fig. 1 Fig1:**
[figure not shown]
Consort diagram. *PRB* Prescriber Recruitment Bundle

### Randomization and consent procedures

The first stage of the block randomization within each state is to develop sampling matched organizations from those that agreed to participate, based on their current use of PRB practices (i.e., number of PRB practices being used 0–7) and whether they were currently prescribing buprenorphine (i.e., yes or no). As a result, 11–13 matched pairs are identified per state. For Ohio and Wisconsin, one matched pair will have two intervention sites to one control site, due to the overall uneven number (*n* = 23). A random number generator is utilized to assign organizations within each pair into one of the two study conditions. Following randomization, study staff will provide University of Wisconsin Institutional Review Board approved study information sheets to staff participants. No visible concealment will be applied. Blinding of participants and researchers is considered logistically infeasible.

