**Fig. 2 Fig2:**
[figure not shown]
PRB implementation sequence (during the 24-month intervention period). *OUD* opioid use disorders, *PRB* Prescriber Recruitment Bundle, *MAT* Medication-Assisted Therapy

During the planning phase, key components of the PRB implementation process (designed based on the evidence-based NIATx organizational change model [38, 39] include (1) defining the aim through a briefing between the executive sponsor and a project coach provided by the research team, (2) assessing PRB baseline to measure level of use of the different PRB practices and document the existing buprenorphine slots availability and extended-release naltrexone capacity, and (3) training leadership and prescriber recruiters to develop and implement an organizational change or a new practice from the bundle. The training will include all organizations within the state that were randomized to the intervention arm to encourage cross-organizational sharing. After the planning phase, a 20-month rollout phase occurs that includes (4) monitoring progress in increasing the number of buprenorphine slots, extended-release naltrexone capacity, and use of the PRB; (5) pilot testing of changes to implement and enhance PRB implementation using the evidence-based Plan-Do-Check (or measure)-Act approach [40]; and (6) sustaining successful changes by implementing a plan to institutionalize gains and avoid reverting to the old system.

Throughout the planning and rollout phases, each organization will have a coach. The coach is an expert in prescriber recruitment, OUD treatment, and organizational change who supports treatment organizations as they make, sustain, and spread PRB practices. Coaches help organizations think through key issues, offer process improvement training, and suggest changes during monthly coaching calls and e-mails as needed.

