### Timeline

During project months 1 to 18, the study team will design the PRB intervention, complete IRB approval, and identify and recruit treatment organizations. In months 14 to 18, the study team will collect baseline data on number of assigned and open buprenorphine slots and extended-release naltrexone capacity. In months 15 to 42, the study team will implement the study arm interventions and collect outcome data on the 24-month staggered start intervention. During months 37 to 52, the study team will collect quantitative data on the sustainability of the changes. Data analysis, publication development, and dissemination of findings will occur at several points, but primarily during months 53 to 60.

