For the primary outcome analysis, mixed-effects models (random effects due to organization and fixed effects due to study arm and time) will be used for data analysis of the monthly number of assigned and open buprenorphine slots per organization, estimated extended-release naltrexone capacity, buprenorphine use, and extended-release naltrexone use. A number of organizational characteristics found by Knudsen et al. [45] to affect the presence of physicians in addiction treatment setting, including facility type, services offered, and organizational size, will be included in the models as covariates to properly and efficiently estimate the effect of PRB. We will examine the PRB effect at each time point using cross-sectional multilevel models and will also implement growth curve models across time that include the PRB effect, time, and PRB*time, as well as time-varying covariates and organizational characteristics. The available and open buprenorphine slots, extended-release naltrexone capacity, buprenorphine use, and extended-release naltrexone use will be measured repeatedly for the same subjects, and it is expected that these values will be correlated over time. Therefore, instead of assuming an independence (i.e., zero correlation) or a compound symmetry covariance structure (i.e., a constant correlation regardless of the proximity of measurement time points), we will allow errors to be auto-correlated or Toeplitz structured, denoted as AR(p) or TOEP(p), in the growth curve models. This can be done by allowing additional parameters in the mixed-effects model error structures that represent the correlation between the adjacent measures of outcomes, and is reduced as the measures become further apart [46]. For the meditational analysis, we will examine the mediating effects of resources dedicated to physician satisfaction and PRB implementation fidelity through a causal mediational analysis. Each of the factors will be aggregated at the organizational site level and measured using mixed-effects models. Through a mediation analysis [47, 48], we can estimate the direct (buprenorphine slots, extended-release naltrexone, buprenorphine use, and extended-release naltrexone use with and without PRB) and indirect effects (resources dedicated to prescriber recruitment, staff prescriber satisfaction, and PRB implementation fidelity) of the PRB on the outcome measures. Using the R package “mediation,” we will estimate the causal mediation effects, examine moderated mediation effects, and conduct sensitivity analysis at each time point as well as across time [49].

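### The statement that researchers cannot be blinded makes no exception for those who clean and model the outcome counts, who could be masked at almost no cost

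*Protocol article*

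**What the plan says.** All references are to the protocol article.

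- **Randomization and consent procedures:** "No visible concealment will be applied", followed by "Blinding of participants and researchers is considered logistically infeasible". Neither sentence separates site staff, coaches, data handlers and analysts.
- **Trial design:** the intervention is delivered through the "evidence-based NIATx organizational change model developed by our research center".
- **Interventions (text after Fig. 2):** each intervention site works with "a project coach provided by the research team".
- **Data analysis:** three organizational covariates (type of facility, its services and its size) are named as going into the models, as examples from a longer set. Time-varying covariates are mentioned but not named. On the error structure: "we will allow errors to be auto-correlated or Toeplitz structured, denoted as AR(p) or TOEP(p), in the growth curve models". Effects are to be examined both at each time point and through growth curves.
- **Timeline:** "Data analysis, publication development, and dissemination of findings will occur at several points, but primarily during months 53 to 60". Collection of sustainability data runs to month 52.
- **Abstract:** the primary outcomes are monthly counts reported by the sites themselves.

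**The concern.** Logistics is a good reason for not blinding sites and coaches. It is not a reason for leaving the data handler and statistician unmasked. They work on a file with one row per site and month, and replacing the arm label with a code needs nothing from the sites.

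Two steps involve judgement. The first is cleaning: deciding whether an implausible slot count stands, or whether a late correction is accepted. The second is model building: covariates beyond the three named, the covariance structure, the coding of time, and which effect is tested. If the people making these decisions can see which arm is the intervention, the decisions can drift towards the favourable answer without any intent. The team's links to the intervention make the safeguard worth having. Sites are unblinded and supply the outcome, so cleaning and analysis are the steps where masking is still possible.

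This is a rule that the article states, not a detail it leaves to another document. A statistical analysis plan that is not shown could fix the model, but it would not by itself correct this sentence.

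**Working it through.** **1. Does masking touch any planning figure?** Inputs from the Sample size section: 28 sites per arm after 20% attrition (J = 56), n = 150 slots per site, ICC ρ = 0.10, d = 0.30, α = 0.05 (two-sided assumed), stated power .93.

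- Noncentrality: λ = J·d² / {4[ρ + (1 − ρ)/n]} = 56 × 0.09 / {4 × (0.10 + 0.90/150)} = 5.04 / 0.424 = 11.89. Power from the noncentral F(1, 54) is 0.923.
- Normal version: SD of a site mean = √[(1 + 149 × 0.10)/150] = √0.106 = 0.326. SE of the difference = 0.326 × √(2/28) = 0.087. Power = Φ(0.30/0.087 − 1.96) ≈ 0.932.

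The stated .93 reproduces. The arm coding enters none of these inputs, so masking leaves sample size, power and α unchanged.

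**2. To whom does the stated reason apply?**

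| Role | Sees the arm unavoidably? | Source |
|---|---|---|
| Site staff | Yes: coached, or website only | Trial design; Interventions |
| Coaches | Yes: they deliver the intervention | Interventions |
| Whoever cleans counts and fits primary models | No: can use a coded variable | role not described; statement has no exception |
| Mediation analysis | Yes: uses PRB fidelity | Data analysis |
| Qualitative work on implementation | Yes: selects intervention sites by fidelity | Data collection and measures |

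The infeasibility claim fails for the third row only.

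**3. Can the harm be sized?** An obvious attempt is to count false positives when the most favourable model is chosen. The setting is assumed: no true effect, 35 v 35 sites, one mean per site, least squares on arm plus any subset of three covariates (8 models), covariates explaining 20% or 40% of variance, 6,000 null trials.

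| | R² = 0.2 | R² = 0.4 |
|---|---|---|
| Full model fixed in advance, two-sided | 4.8% | 4.6% |
| Best of 8, two-sided | 9.7% | 12.0% |

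To see what masking contributes, compare two selection rules by their false positives in the intervention's favour (nominal 2.5%). Two runs were made.

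| | R² = 0.2 | R² = 0.4 |
|---|---|---|
| Label known: take any favourable significant model | 4.8%, 4.9% | 6.7%, 6.2% |
| Label masked: take the smallest two-sided p | 4.8%, 4.9% | 6.7%, 6.2% |

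The rules agree because they can differ only in a trial where some models are significant in one direction and others in the opposite direction. The inflation therefore comes from choosing among models. A lock removes it; dummy codes alone do not. A 34-month version (56 sites, one outcome) reached 0.21–0.25 when the tested effect could also be chosen, against 0.050–0.055 for one fixed analysis. That too is best-of-many selection. In addition, the Data analysis section commits to the three named covariates, so the fixed full model is the row nearest to the text.

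Masking itself protects record-level cleaning and directional judgement. The documents hold no figure from which that part can be sized.

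**4. Would the mask hold?** Florida has 24 sites (12:12). Ohio and Wisconsin have 23 each, with one set of two intervention sites to one control: 10 pairs plus that set give 12:11 in each state. The total is 36:34, whereas the Participants section gives 35:35. Those passages need reconciling. If 12:11 stands, arm counts by state could reveal the code.

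**The case against.** The strongest case on the other side has four parts.

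- **The text does not say that coaches or developers analyse the data.** A reader might infer it from the shared first person and the unqualified sentence. No analyst is named, so this remains an inference. The point here rests only on the absence of an exception.
- **Early arm comparisons are not stated.** A reader might take the Timeline to mean looks at outcomes by arm before month 52. It does not say what the early analyses are. The article describes other work that could fill them: the baseline comparison, and qualitative analysis that starts as soon as interviewing does.
- **The open modelling choices may be closed elsewhere.** The order p, autoregressive or Toeplitz errors, the full covariate list and the cleaning rules commonly belong in a statistical analysis plan, which is not shown. Their absence is not a fault. If such a plan fixes them in advance, most of the modelling risk goes.
- **False-positive rates of roughly 10–15% do not measure missing masking.** This is correct, as the comparison of selection rules shows, and no such figure should be attached to the point.

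All four stand, and they limit the weight. They do not rescue the sentence, which gives a logistical reason for excluding a safeguard to which logistics is no obstacle.

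**Conclusion.** The concern holds in a limited form. The infeasibility statement is too broad: it is right for sites and coaches, and wrong for those who clean the outcome file and fit the primary models. Correcting it is a cheap improvement of minor to moderate weight, justified by the team's role as developer of the change model and supplier of coaches. No numerical bias can be given, and no planning figure changes.

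The conclusion assumes that the unqualified wording means what it says, so that no masked analyst is planned. That masking costs almost nothing is a methodological judgement, not a figure from the documents. Masking would not address reporting by unblinded sites and does not extend to the mediation or qualitative parts.

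**What to change.** Replace the blinding sentence with text to this effect:

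- Sites and coaches cannot be blinded.
- Those who clean the monthly outcome counts and fit the primary models work with dummy arm codes. They have no access to coaching records or PRB fidelity data until the outcome data are cleaned and the primary model is locked.
- The lock covers covariates beyond the three named, the covariance structure, the time coding and the tested effect. It is made before any arm contrast is examined, coded or not.
- Analyses before the lock are limited to baseline, pooled or qualitative results.

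The cost is a short protocol change and one coded variable, with no added data. The key can be held by someone already on the team who does not clean or model the outcomes. The Trial status section says that recruitment is nearly complete and baseline collection has begun, so the change can still precede outcome analysis.

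The downsides are that no quantitative arm comparison can be released before the lock, and that masking may be imperfect if the effect is large or if uneven arm counts in Ohio and Wisconsin give the code away.
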